Aged ≥18 years at the time of signing the informed consent form. Suffering from uncontrolled, severe CHE defined as the presence of *both* of the following criteria: (A) PGA score of severe.^27^ (B) Resistance to treatment with potent topical corticosteroids for ≥4 weeks prior to the point of eligibility screening. Provided written informed consent. Expected to comply with treatment and protocol schedule.	**Skin related:** Patients who have a clinically suspected infection (fungal, bacterial or viral) as cause for dermatitis of the hands. Patients with known clinically relevant allergic contact dermatitis of the hands unless they had made a reasonable effort to avoid the contact allergen. Patients suffering from atopic eczema covering more than 10% of body surface (excluding hands). Patients who have skin conditions worsened by the sun that is, do not tolerate UV-light (eg, lupus erythematosus, porphyria). **Treatment related:** Patients who have received phototherapy/photochemotherapy in the last 3 months prior to randomisation Patients who have received systemic vitamin A derivatives or other systemic immunosuppressants, for example, methotrexate or biologics treatment for HE in the last 3 months prior to randomisation. Patients who have received ciclosporin A or systemic glucocorticoid steroid treatment for HE within 1 week prior to randomisation. Patients receiving topical calcineurin antagonist treatment within 1 week prior to randomisation. Patients receiving concomitant treatment with tetracyclines, or medication with potential for drug–drug interaction with alitretinoin (eg, CYP3A4 inhibitor ketoconazole) that cannot be suspended or switched to an acceptable alternative Patients receiving concomitant treatment with relevant photosensitisers, when this treatment cannot be suspended for the duration of the intervention or switched to an acceptable alternative Patients with a history of melanoma skin cancer, or patients with a history of non-melanoma skin cancer depending on history, location and ‘severity’ of the non-melanoma skin cancer based on experience from routine practice. Patients who have received prior treatment with arsenic agents or ionising radiation in the treatment area (eg, hands). **General:** If female: (1) Lactating (2) Of childbearing potential (CBP): With positive pregnancy test (absence of pregnancy will be confirmed with a negative pregnancy test before randomisation). (2) Unwilling to follow pregnancy prevention programme measures* while receiving treatment and after the last dose of protocol treatment as indicated in the relevant SmPC. Patients with hepatic insufficiency (alanine aminotransferase and/or aspartate aminotransferase >2.5 times the upper limit of normal), known severe renal insufficiency, uncontrolled hyperlipidaemia (for all of the following: triglycerides, cholesterol and/or LDL cholesterol) or uncontrolled hypothyroidism in the 12 weeks period prior to randomisation. Patients with known hypersensitivity to peanut, soya or vitamin A derivatives or with rare hereditary fructose intolerance as determined by patient history. Patients currently suffering from hypervitaminose A as directed by clinical symptoms or patient history. Patients previously participated in the ALPHA trial.

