### Treatment pathway: criteria of response

Responders, defined as a PGA score of clear/almost clear at 12 weeks post planned start of treatment, will discontinue randomised treatment.

Partial responders, defined as a PGA score of mild/moderate at 12 weeks post planned start of treatment, will continue with randomised treatment for up to a further 12 weeks. During this second 12 weeks treatment period patients will be monitored at 4 weekly intervals and randomised treatment can be stopped at any time if the participant responds, or symptoms worsen and in the opinion of the treating clinician there is no clinical benefit to continuation.

Non-responders, defined as a PGA score of severe at 12 weeks post planned start of treatment, will discontinue randomised treatment.

In line with standard clinical practice, cessation or alteration of regimens at any time will be at the discretion of attending clinicians or the participants themselves. All randomised treatment will be discontinued at the maximum 24 weeks treatment period and participants will continue to receive ‘standard clinical practice’ and follow-up monitoring until the end of the follow-up period.

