### Data collection

Clinical data and patient reported data will be collected at baseline, every 4 weeks to week 24 and 8 weekly thereafter to week 52. At each assessment a review of medication diaries will be conducted to obtain data on HE topical corticosteroid usage and any HE treatment received (in conjunction with clinical records review). Reportable adverse reactions will be collected and will exclude the following, providing they are non-serious, because they are known and common reactions; headaches and dry skin on regions of the body other than hands for alitretinoin, and mild to moderate erythema or itching of skin in PUVA treated skin locations for the PUVA arm). For participants recruited from October 2019, the follow-up period ends at 24 weeks post planned start of treatment. A full schedule of assessments is provided in online supplemental material 3.

10.1136/bmjopen-2021-060029.supp3Supplementary data

Data will be monitored for quality and completeness by the CTRU. Missing data will be chased until received, confirmed as not available or the trial is at analysis. Data received will be linked anonymised and entered onto a secure database at CTRU in accordance with the 2018 Data Protection Act. Photographs taken will be transferred immediately by secure email to CTRU and immediately deleted from the camera once confirmation of receipt is received by the research team. The CTRU and sponsor reserve the right to intermittently conduct source data verification exercises on a sample of participants, which will be carried out by staff from the CTRU or Sponsor.

Details of biological sample management is available in online supplemental material 4.

10.1136/bmjopen-2021-060029.supp4Supplementary data

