### Outcomes

#### Primary outcome measure

The primary outcome is measured as the natural logarithm of the HECSI^26^ at 12 weeks postplanned start of treatment. The HECSI is a validated scoring system used to clinical assess the severity and extent of HE.^26^

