### Primary endpoint analysis

#### Primary analysis

A multivariable multilevel repeated measures linear regression model will be fitted to the primary endpoint, log_e_(HECSI), adjusting for minimisation factors duration of disease, clinical phenotype, DLQI, presence of specific IgE to inhalant or other relevant allergens and ethnicity, and the covariates: smoking history, BMI, foot involvement,^37 38^ filaggrin loss of function mutation, baseline log_e_(HECSI) and treatment group. Centre, participant and participant–time interaction will be fitted as random effects. The relative difference in the HECSI score at 12 weeks post planned start of treatment, corresponding 95% CIs and p values will be reported.

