### Secondary endpoint analyses

Multivariable multilevel repeated measures linear regression models of log_e_(HECSI score), mTLSS, DLQI, PeDeSi and PBI-HE, and a multilevel repeated measures ordinal logistic regression model of the PGA over time will be fitted adjusting for the minimisation factors, covariates as for the primary endpoint analysis, corresponding baseline measurement and treatment group, as fixed effects. Centre, participant and participant-time interaction will be fitted as random effects. The parameter estimates, corresponding 95% CIs and p values will be reported; contrasts for the treatment effect at 24 and 52 weeks postplanned start of treatment will also be reported.

A Cox proportional hazards (PH) model (after confirming the PH assumption is valid) will be fitted to time to relapse adjusting for minimisation factors and covariates as for the primary endpoint analysis.

AEs and SAEs classified as related to treatment, HE or resulting from administration of any research procedures will be reported descriptively.

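### As usually fitted, the participant and participant–time random effects do not let the variance of log HECSI differ freely by visit, so the week-12 confidence interval and p value may be too narrow

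*Protocol article*

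**What the plan says.** **Primary model.** "The primary outcome is measured as the natural logarithm of the HECSI" at week 12 (Primary outcome measure). Under Primary analysis, "A multivariable multilevel repeated measures linear regression model will be fitted to the primary endpoint", adjusted for minimisation factors and covariates that include baseline log HECSI. The random part is given in one sentence: "Centre, participant and participant–time interaction will be fitted as random effects". On output: "The relative difference in the HECSI score at 12 weeks post planned start of treatment, corresponding 95% CIs and p values will be reported". The article does not say whether time is continuous or by visit, what covariance the random effects have, or which visits enter.

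**Over-time models.** Secondary endpoint analyses lists separate linear models of log HECSI and four other scores, with contrasts at weeks 24 and 52, and uses the same structure: "Centre, participant and participant-time interaction will be fitted as random effects".

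**Visits.** Data are collected at baseline and then "every 4 weeks to week 24 and 8 weekly thereafter to week 52" (Data collection). Follow-up ends at week 24 for those recruited from October 2019.

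**Pathway.** Entry requires a "PGA score of severe" (Eligibility criteria, Table 1). At week 12 responders stop randomised treatment and partial responders continue for up to 12 more weeks (Treatment pathway: criteria of response). For the rest: "Non-responders, defined as a PGA score of severe at 12 weeks post planned start of treatment, will discontinue randomised treatment".

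**Variability.** The only figures are the coefficients of variation (CV) under Sample size, which refer to the week-12 score. No variance by visit is given.

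**The concern.** The issue is the covariance part of the model. It remains even if visit and treatment-by-visit terms are in the fixed part.

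The design suggests that variance is not constant. All participants start severe and baseline log HECSI is a covariate, so the spread around the model should be small early and grow as participants diverge. At week 12, the primary time point, treatment changes for responders and non-responders. The variance may keep rising afterwards, level off or fall.

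If the fitted structure averages over visits with smaller variance, the fitted week-12 variance is too low. The interval for the primary ratio is then too narrow, and the two-sided 5% level stated under Sample size is exceeded.

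**Working it through.** **1. The plan's own figures.** Inputs from Sample size: ratio 1.3, so ln 1.3 = 0.2624; 80% power; two-sided 5%; CV 1.175 to 1.7; 20% attrition. The log SD is √ln(1 + CV²), and n per arm is 2(1.96 + 0.8416)²·SD²/0.2624².
- CV 1.175: SD 0.931, 198 per arm, 396 in total, 396/0.8 = 495 (stated 500).
- CV 1.7: SD 1.166, 310 per arm, 620 in total, 620/0.8 = 775 (stated 780).

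Both reproduce. Nothing below changes them.

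**2. What each reading allows.**
- Continuous time, with random intercept, linear slope and constant residual: Var(t) = s0² + 2·s01·t + s1²·t² + se². The second derivative is 2·s1² ≥ 0, so the curve is convex and has no interior maximum.
- Time by visit, with one common participant–time variance: each participant has one score per visit, so this effect merges with the residual. Var = sb² + (sc² + se²) at every visit and the covariance is sb². This is compound symmetry.
- Time by visit with unequal variances also fits the sentence, and can hold any profile.

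**3. Consequence at week 12.** With treatment-by-visit means, complete data and model-based standard errors, the week-12 contrast is the difference in week-12 means. Its SE ratio (fitted to true) is r = √(fitted variance/true variance), and the two-sided type I error is 2Φ(−1.96·r).

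**4. Assumed profiles.** SDs are relative to week 12: the week-4 value rises linearly to 1 at week 12, moves linearly to the week-24 value, then stays flat. Visits are weeks 4, 8, 12, 16, 20, 24, 32, 40, 48 and 52. The assumed correlation is 0.3 constant plus 0.55 decaying by a factor of 0.8 per 4 weeks. Each structure is fitted by minimising log|Vm| + tr(Vm⁻¹V). Entries are r and type I error.

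| Visits used | SD at weeks 4 / 12 / 24 on | Intercept and slope | Compound symmetry |
|---|---|---|---|
| 4–52 | 1 / 1 / 1 | 1.006, 4.9% | 1.000, 5.0% |
| 4–52 | 0.9 / 1 / 0.9 | 0.943, 6.5% | 0.926, 7.0% |
| 4–52 | 0.8 / 1 / 0.8 | 0.881, 8.4% | 0.853, 9.5% |
| 4–52 | 0.7 / 1 / 1 | 0.935, 6.7% | 0.960, 6.0% |
| 4–52 | 0.7 / 1 / 1.1 | 0.975, 5.6% | 1.023, 4.5% |
| 4–24 | 1 / 1 / 1 | 0.967, 5.8% | 1.000, 5.0% |
| 4–24 | 0.9 / 1 / 0.9 | 0.916, 7.3% | 0.942, 6.5% |
| 4–24 | 0.8 / 1 / 0.8 | 0.866, 9.0% | 0.886, 8.2% |
| 4–24 | 0.7 / 1 / 1 | 0.882, 8.4% | 0.932, 6.8% |
| 4–24 | 0.7 / 1 / 1.1 | 0.905, 7.6% | 0.969, 5.8% |
| 4–12 | 1 / 1 / – | 1.010, 4.8% | 1.000, 5.0% |
| 4–12 | 0.9 / 1 / – | 1.005, 4.9% | 0.951, 6.2% |
| 4–12 | 0.8 / 1 / – | 1.000, 5.0% | 0.904, 7.7% |
| 4–12 | 0.7 / 1 / – | 0.995, 5.1% | 0.859, 9.2% |

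Steeper profiles give more: 0.7 / 1 / 0.7 gives 10.3–12.5% when later visits are used.

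**5. Cross-check.** A second set uses SDs 0.65, 0.82 and 0.944 at weeks 4, 8 and 12 (0.944 corresponds to CV 1.2), three correlation structures and visits 4–52.
- Flat after week 12: 6.7–6.9% (slope), 6.0% (compound symmetry).
- Fall to 0.80 by week 24: 8.5–8.9% and 8.9%.
- Fall to 0.75: 9.2–9.6% and 10.1%.
- Weeks 4–12 only: about 5% and 9.1%.

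**6. On the reported scale.** With log SD 0.9445 and 200 evaluable per arm (500 × 0.8/2), the true SE is 0.9445·√(2/200) = 0.0945 and the 95% half-width is 1.96 × 0.0945 = 0.185, a factor of 1.20 either side of the ratio. At r = 0.881 the half-width is 0.163, a factor of 1.18.

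**7. With variance free by visit,** r = 1.00 and the type I error is 5% under every profile.

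**The case against.** The strongest reply is that the error needs conditions the article does not state. Four parts of it have weight.

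- **A reader might infer that the variance peaks at week 12.** The documents do not show this. Partial responders continue treatment. On the log scale, further clearing, relapse at different times and varied later therapy could all keep variance rising. This stands: the peak is a possibility only.
- **A reader might infer that the stated model cannot represent the variance at all.** That is also too strong, because by-visit effects with unequal variances fit the same sentence. This stands too. In addition, compound symmetry supposes a listed random effect that is aliased with the residual, which is the less natural intention.
- **The primary model may stop at week 12.** A separate over-time model with contrasts at weeks 24 and 52 suggests this without proving it. A random slope would then be adequate. Compound symmetry would not, if variance rises.
- **The detail belongs in the statistical analysis plan,** which Statistical methods promises before any comparative analysis. Leaving time coding and visit window to that plan is no fault. However, the article does fix the random effects, and an analysis plan that follows it inherits them. The point concerns that stated choice.

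**Conclusion.** The point holds as a conditional weakness of the stated model. It is not a demonstrated error in the primary p value.

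On the two usual readings, type I error is about 6–9.5% if variance rises to week 12, then flattens or falls moderately, and later visits enter. Under compound symmetry on weeks 4–12 it is about 6–9%.

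There is no material error in these cases:
- variance is constant, apart from about 5.8% for a slope fitted to weeks 4–24;
- variance keeps rising and visits to week 52 are used (4.5–5.6% in the table; a slope fitted only to week 24 gives 7.6%);
- a random slope is fitted to weeks 4–12 only;
- variances by visit are already allowed.

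Every figure rests on assumed SD and correlation profiles, treatment-by-visit means, complete data and model-based standard errors. The direction follows from the algebra once variance has the assumed shape; the size cannot be established from the article.

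**What to change.** **Primary analysis.** Fit visit as a factor with an unstructured within-participant covariance over the visits up to week 12, in place of the participant and participant–time random effects. Keep centre as a random effect. State robust (sandwich) standard errors as the fallback if the model does not converge. Weeks 4, 8 and 12 need 3 × 4/2 = 6 covariance parameters, against about 400 evaluable participants at the minimum sample size (500 × 0.8).

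**Secondary linear models.** Let the residual variance differ by visit, or use robust standard errors.

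**Cost.** A change of wording and of one model statement, a few extra covariance parameters, and a fallback to prespecify. No new data are needed and the sample size is unaffected.

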### Secondary endpoint analyses

Multivariable multilevel repeated measures linear regression models of log_e_(HECSI score), mTLSS, DLQI, PeDeSi and PBI-HE, and a multilevel repeated measures ordinal logistic regression model of the PGA over time will be fitted adjusting for the minimisation factors, covariates as for the primary endpoint analysis, corresponding baseline measurement and treatment group, as fixed effects. Centre, participant and participant-time interaction will be fitted as random effects. The parameter estimates, corresponding 95% CIs and p values will be reported; contrasts for the treatment effect at 24 and 52 weeks postplanned start of treatment will also be reported.

A Cox proportional hazards (PH) model (after confirming the PH assumption is valid) will be fitted to time to relapse adjusting for minimisation factors and covariates as for the primary endpoint analysis.

AEs and SAEs classified as related to treatment, HE or resulting from administration of any research procedures will be reported descriptively.

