## Methods and design

### Objectives

The overall aim of the trial is to determine the clinical and cost effectiveness of alitretinoin and immersion PUVA when used in conjunction with concomitant topical corticosteroids, emollients and patient education for the treatment of severe CHE which is unresponsive to treatment with potent topical corticosteroids alone.

The primary objective is to compare alitretinoin and immersion PUVA as first-line therapy in terms of disease activity at 12 weeks post planned start of treatment.

The secondary objectives are to compare alitretinoin to PUVA over 52 weeks postplanned start of treatment in terms of:

Disease activity over time.Time to relapse.QoL and patient benefit over time.Within trial and long-term cost-effectiveness.Safety.Educational need for patients.

Exploratory objectives are to:

Compare scoring systems Hand Eczema Severity Index (HECSI), modified Total Lesion Symptom Score (mTLSS), Dermatology Life Quality Index (DLQI) and physician’s global assessment (PGA) used to monitor treatment response.Explore whether response to first line treatment is affected by: duration of disease, clinical phenotype, disease severity, presence of atopy, smoking history, body mass index (BMI), foot involvement and Filaggrin loss of function mutation and other potential emerging mutations affecting skin barrier or response to treatment.Collect pilot data on clinical effectiveness of second line therapies.Explore treatment responses in HE subgroups defined by molecular inflammatory mediators.Compare alitretinoin and PUVA in terms of time in remission.Compare alitretinoin and PUVA in terms of nail assessment.Explore the use of the photography guide for patients from minority ethnic groups.

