### Blinding

The trial is open-label as participants and investigators cannot be blinded to treatment allocation due to the nature of the PUVA intervention. However, the assessment of the HE severity scores will be undertaken by a clinical assessor (research/dermatology nurse or a clinician) who is blinded to the randomised treatment and where possible, will be the same person at each assessment of a participant. Participants will be reminded not to reveal which treatment they have received to the blinded assessors in order to preserve blinding.

Photographs will be taken for 20% randomly identified, consenting participants of white ethnicity. Photographs will be taken from all consenting participants of from minority ethnic groups at each centre. Photographs will be taken at baseline and 12 weeks post planned start of treatment. A blinded central review of the photographs will be conducted by a central review panel.

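### Safety is to be compared between arms, but only events classified as related are to be reported in an open-label trial, so the comparison may depend on attribution

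*Protocol article*

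**What the plan says.** All references are to the protocol article.

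- **Objectives.** Safety is a between-arm objective. The list opens "The secondary objectives are to compare alitretinoin to PUVA over 52 weeks postplanned start of treatment in terms of" and includes, run together by the text extraction, "Within trial and long-term cost-effectiveness.Safety.Educational need for patients".
- **Secondary endpoint analyses.** The only safety output described is: "AEs and SAEs classified as related to treatment, HE or resulting from administration of any research procedures will be reported descriptively". The condition covers AEs and SAEs alike. It admits three classes of event: linked to treatment, linked to the eczema, or caused by a research procedure.
- **Data collection.** The only sentence on recording safety events reads "Reportable adverse reactions will be collected and will exclude the following, providing they are non-serious, because they are known and common reactions". One arm's exceptions are "headaches and dry skin on regions of the body other than hands for alitretinoin". The other arm has its own list, namely "mild to moderate erythema or itching of skin in PUVA treated skin locations for the PUVA arm".
- **Blinding.** "participants and investigators cannot be blinded to treatment allocation". A blinded assessor is provided for the eczema severity scores. No blinded step for judging the cause of an adverse event is described.
- **Interventions.** Alitretinoin is taken by mouth. PUVA is given by soaking the hands and exposing them to UVA.

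**The concern.** A count restricted to related events is the product of two things: how often events happen, and how often someone decides that they belong to one of the admitted classes. Randomisation protects the first. Nothing in the article protects the second, because those treating the patient know the arm. The two treatments also differ in kind. An event away from the hands may be put down to an oral systemic drug more readily than to a local hand treatment, and so may be counted in one arm and left out in the other.

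The related-event tables are the only safety output described for a comparative objective. If attribution differs by arm, they can show a difference where the event rates are equal, or conceal a real one. The filter reaches serious events too, where an all-cause count is the usual safeguard.

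There is also a smaller, textual matter. The section on collection and the section on reporting do not describe the same set of events, so it is unclear what the report can contain.

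**Working it through.** **1. No stated figure to reproduce.** The article gives no expected event rate and no precision for safety. Its sample-size figures concern the HECSI score and have no bearing here.

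**2. The sections side by side.**

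| Question | Section | Answer in the text |
|---|---|---|
| Is safety compared between arms? | Objectives | Yes, over 52 weeks |
| Which events are reported? | Secondary endpoint analyses | AEs and SAEs classified as related to treatment or eczema, or caused by research procedures |
| Which events are collected? | Data collection | Reportable adverse reactions, less named non-serious ones |
| Who knows the arm? | Blinding | Participants and investigators |
| What is assessed blind? | Blinding | Eczema severity scores |
| Who classifies relatedness? | None | Not stated |

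An adverse reaction, in ordinary usage, is an event caused by the treatment. Events due to the eczema or to a research procedure are not reactions to the treatment, so the collection wording does not cover two of the three reported classes. The arm-specific exceptions under Data collection are a separate matter: they apply only to non-serious reactions and do not touch SAEs. They do imply that whoever applies them knows the allocation.

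**3. How attribution enters the comparison.** Let p be the true event risk in an arm and a the probability that an event is classified as related.

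Reported risk = p × a

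Reported ratio = (p₁ × a₁) / (p₂ × a₂) = true ratio × (a₁ / a₂)

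If the true risks are equal, the reported ratio is a₁ / a₂, whatever the value of p.

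**4. Illustration.** Inputs: 441 participants randomised at submission (Trial status) in a 1:1 ratio (Allocation), so about 220 per arm. The true risk of 20% in both arms and the attribution probabilities are assumptions; the documents give neither. True events are 220 × 0.20 = 44 per arm.

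| Attribution, alitretinoin v PUVA (assumed) | Reported events | Reported risk | Ratio |
|---|---|---|---|
| 60% v 60% | 26.4 v 26.4 | 12% v 12% | 1.0 |
| 60% v 50% | 26.4 v 22.0 | 12% v 10% | 1.2 |
| 70% v 50% | 30.8 v 22.0 | 14% v 10% | 1.4 |
| 80% v 50% | 35.2 v 22.0 | 16% v 10% | 1.6 |
| 70% v 40% | 30.8 v 17.6 | 14% v 8% | 1.75 |

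An all-cause count gives 44 v 44, ratio 1.0, in every row. The effect can also run the other way: a true ratio of 1.2 with attribution of 50% v 60% is reported as 1.2 × 50/60 = 1.0.

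**5. A limit of the illustration.** It models attribution to treatment only. Eczema-related and procedure-related events are also admitted. If these add the same amount c to each arm, the ratio becomes (p·a₁ + c) / (p·a₂ + c), which lies closer to 1 than a₁ / a₂. The table therefore shows the mechanism, not a forecast.

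**The case against.** The strongest case against the point is that a journal article condenses a fuller protocol. Event definitions, SAE recording and the assignment of causality are commonly left to that document, which is not shown. The sentence under Data collection mainly serves to list common reactions that need not be reported. It does not say that nothing else is recorded, and the phrase about events being classified suggests that events are recorded first and sorted afterwards. Reporting is descriptive, so no test can give a false positive. The DMEC reviews safety, and under Trial governance the TSC considers its recommendations after reviews of data by treatment group.

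Much of this stands, and it rules out three stronger readings.

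- A reader might infer that unblinded investigators make the causality judgement. This is plausible, since investigators know the arm, but no sentence says so.
- A reader might infer that unrelated SAEs, or events due to eczema or procedures, are not collected. The article does not show that. It shows only that its two sections use different terms.
- A reader might infer that the safety comparison is biased by a known amount, or that particular symptoms will be attributed unequally. The documents give no attribution rates and no basis for naming such symptoms.

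What the objection does not remove is the stated restriction on the report. The sentence under Secondary endpoint analyses fixes what will be presented, applies the filter to SAEs, and serves a comparative objective in an open trial of unlike treatments. Descriptive rates can mislead as well as tested ones when they are the only answer given. Committee review during the trial does not settle what the final report shows.

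**Conclusion.** The point holds in a limited form. As written, the between-arm safety comparison, including that of serious events, may depend on attribution that differs between an oral systemic drug and a local hand treatment. The direction and size of any bias are unknown. With equal true rates and attribution to treatment as the only route into the table, the spurious ratio is the ratio of attribution probabilities: 1.0 if they are equal, 1.2 for an assumed 60% v 50%, 1.75 for an assumed 70% v 40%. The conclusion rests on two readings of the text: that the relatedness condition applies to SAEs as well as AEs, and that no blinded causality step exists, none being described.

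The mismatch between the collection and reporting sections is a wording inconsistency to be reconciled. It is not evidence that data are missing. The primary endpoint is unaffected, and no error rate is at stake.

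**What to change.** 1. **Secondary endpoint analyses.** Report all recorded SAEs by arm regardless of causality, and make this the main descriptive comparison for the safety objective. Keep the related AEs and SAEs as a subset table, labelled as covering attributed events only.
2. **Data collection and Secondary endpoint analyses.** Reconcile the event definitions, so that the collection wording covers the eczema-related and procedure-related events that the report promises.
3. **If unrelated SAEs have not been recorded so far,** record them from now on and state the limitation in the report.

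Adverse events leading to a dose change should not be used as a further comparator. The Interventions section describes a dose reduction for side effects with alitretinoin, whereas the UVA dose is tailored to each participant throughout, so the term does not mean the same in the two arms.

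If all SAEs are already held, the cost is one table and a change of wording. The downside is a longer SAE listing that includes unrelated events. If they are not held, there is also some added recording, and ascertainment may be incomplete for early recruits, since 441 participants had been randomised at submission against a minimum of 500.
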